### Intervention

To better tailor the reminiscence content to the actual situation of older people and evoke their emotional resonance, the reminiscence content of this study will be obtained through preinterviews with the participants. The interview outline has been formulated by researchers and revised by experts, and the interview results will be taken as the specific content of the reminiscence of older people in this study. The outline of the interview is shown in Table 1.

**Table 1 Tab1:** Interview Outline

Reminiscence Stage	Reminiscence content	Points of interest
Childhood (0–18 years)	1、What experiences from your childhood impressed you more? 2、If you recall, what would you most like to recall? 3、What did you do most of the time during your childhood?	Family Study experience Holidays
Young adulthood (18–25 years)	1、What experiences were special to you during your youth? 2、Do you remember what your first job was? 3、If you recall, what would you like to recall most?	Friendship Education Technology change
Adulthood (25–65 years)	1、What experiences during your adulthood were special to you? 2、What were the major turning points? 3、If you recall, what would you like to recall most?	Spouse Parenting Professional experience
Old age (over 65 years)	1、What experiences are special to you at the moment? 2、Do you have any personal feelings about life? 3、Describe a decisive event in your life	Philosophy of life Looking back

#### Reminiscence therapy

The group will implement group reminiscence therapy with 4 reminiscence phases. Each subgroup will consist of 1 implementer and 6–7 participants and will focus on 1 growth phase once a week for 90 min each time. The implementer will be responsible for guiding and encouraging the group members to freely recall past experiences and ensuring that each participant speaks for at least 10 min. The intervention details are shown in Table 2.

**Table 2 Tab2:** Intervention details

Sessions	Content
1st (week 1)	**Life stage**: Childhood (0–18 years) **Topic**: family, study experience, holidays etc. **Members**: 1 implementer and 6–7 participants. **Duration**:90 min. **Method**: The implementer will be responsible for guiding and encouraging the group members to freely recall past experiences and ensuring that each participant speaks for at least 10 min.
2nd (week 2)	**Life stage**: Young adulthood (18–25 years) **Topic**: friendship, education, technology change etc. **Members**: 1 implementer and 6–7 participants. **Duration**:90 min. **Method**: The implementer will be responsible for guiding and encouraging the group members to freely recall past experiences and ensuring that each participant speaks for at least 10 min.
3rd (week 3)	**Life stage**: Adulthood (25–65 years) **Topic**: spouse, parenting, professional experience etc. **Members**: 1 implementer and 6–7 participants. **Duration**:90 min. **Method**: The implementer will be responsible for guiding and encouraging the group members to freely recall past experiences and ensuring that each participant speaks for at least 10 min.
4th (week 4)	**Life stage**: Old age (over 65 years) **Topic**: philosophy of life Looking back etc. **Members**: 1 implementer and 6–7 participants. **Duration**:90 min **Method**: The implementer will be responsible for guiding and encouraging the group members to freely recall past experiences and ensuring that each participant speaks for at least 10 min.

#### Reminiscence therapy combined with memory specificity training

The process and content of reminiscence therapy is the same as described above, but the researcher will help participants to make their recollections more specific and complete when they recall a particular episode. Prompts that guide recall draw on other research [49] and cover the following areas:

- Details – who/what/where/when.- Five senses – smell/taste/hear/see/touch.- Identity – what does this tell us about you as a person?- Positive themes – what was good about this event for you?- Generalization of positive themes – does this link to other activities you have done? How?- Future planning – what steps could you take to repeat this activity?

#### Usual care

All participants will receive usual care, and common nursing home routines are shown in Table 3.

**Table 3 Tab3:** Routine care

Life Care	Recreational activities
1. Cleanliness and hygiene	1. Tea ceremony
2. Sleep care	2. Handcrafted
3. Dietary care	3. Calligraphy
4. Excretion care	4. Ping pong
5. Safe care	5. Chorus

### Outcome measures

See Table 4 for an overview of all measurement instruments and timepoints for older people.

**Table 4 Tab4:** Overview of instruments per assessment

Measures	T0	T1	T2	T3	T4	
Demographics	×					
GDS	×	×	×	×	×	
ATM	×	×	×	×	×	
RRS	×	×	×	×	×	
IPA	×	×	×	×	×	
T0: baseline, T1: immediately postintervention, T2: 1month postintervention, T3: 3 months postintervention, T4: 6 months postintervention.						

#### Depressive symptoms in older people

Depressive symptoms in older people will be measured by the Geriatric Depression Scale. This scale was developed by Yesavage [50] et al. as a special depression screening scale for people over 56 years of age, and each examination takes approximately 15 min. It consists of 30 questions and four factors: ① unhappiness ② apathy and anxiety ③ loss of hope and morale ④ memory loss and reduction of social activity. Ten of the 30 items are scored in the reverse direction and 20 in the positive direction. The total score is 0–30, with higher scores indicating more severe depression. Scores of 0–10 are normal, scores of 11–20 indicate mild depression, and scores of 21–30 scores indicate moderate and severe depression. The Cronbach coefficient of the GDS is > 0.85, the retest reliability is > 0.73, and the reliability is > 0.84, with good internal consistency and stability [51].

#### Autobiographical memory

Participants’ autobiographical memory will be measured by the Autobiographical Memory Test. The Autobiographical Memory Test was developed by Williams and Broadbent in 1987 [52] and is a test that is currently widely used in clinical research; this assessment utilizes a cue word technique in which subjects review past personal experiences through cue words that contain five positive cue words, five neutral words, and five negative cue words. Participants will be given two neutral practice words to practice before the formal test. They will be asked to verbally recall memories related to cue words within 1 min during the formal administration of the test, and the implementer will record the recollections in the form of a transcript. The scoring will be performed by two researchers who are not involved in the administration of the test. The two scorers will classify the participants’ recollections into four categories: specific memory, generalized memory, vocabulary association or nonrecollection and nonresponse, and the scoring will be based on the number of cue words recalled by the participants. Since Chinese scholars have translated the cue words in this test into Chinese, composed a vocabulary database and rated the valence of the vocabulary, the Chinese version of the ATM will be used in this study [53], which has a high internal consistency and a reliability test Kappa coefficient of 0.81–0.95 [54]. Cue words that will be used in the assessments and training are shown in Table 5.

**Table 5 Tab5:** Cue words

pre-test	post-test	follow-up
Strong	Deep Love	Honest
History	Books	Relaxed
Fear	Sadness	Friendly
Security	Interesting	Guilty
Individual	Oval	Nervous
Failure	Reject	Desperate
Excitement	Lively	Patience
Caution	Bread	Agile
Solitude	Doubt	Culture

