Currently, reminiscence therapy combined with memory-specific training is mainly used in the psychological treatment of cancer patients in palliative care, and its effectiveness needs further validation, as randomized controlled trials of Life Review Therapy combined with Memory Specificity Training (LRT- MST) by Gitta Kleijn showed no significant differences between the two groups in terms of anxiety, depression, quality of life and autobiographical memory in cancer patients [41, 42]. However, other studies have shown that reminiscence therapy based on autobiographical memory training can be used in future studies to investigate available, cost-effective, low-intensity treatment options for patients experiencing mood disorders [43, 44]; thus, further investigation of this therapy is warranted.

Based on the national situation that depressed older people are increasing year by year in China, this study aims to implement a randomized controlled trial of reminiscence therapy combined with memory specificity training in a Chinese context to investigate whether this therapy can reduce rumination and improve depressive symptoms in older people and improve their psychological health by improving autobiographical memory. In this study, it is hypothesized that older people who participate in reminiscence therapy combined with memory specificity training will report improved autobiographical memory specificity, less rumination, and significantly lower levels of depressive symptoms at postintervention and follow-up time points than older adults receiving usual care and reminiscence therapy alone; we further hypothesize that these improvements will be maintained for 6 months after the intervention.

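### The Autobiographical Memory Test is inconsistently specified: 15 or 9 cue words, one follow-up list for three visits, words assigned to both assessment and training, and a score not tied to specificity

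*Protocol article*

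**What the plan says.** All references are to the protocol article.

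- **Test length.** The Autobiographical memory section describes a cue-word test with "five positive cue words, five neutral words, and five negative cue words". Table 5, in the same section, prints the lists under three columns: "pre-test post-test follow-up".
- **Occasions.** Table 4 (Outcome measures) marks the memory test at all five assessments. Its footnote defines the last three: "T2: 1month postintervention, T3: 3 months postintervention, T4: 6 months postintervention".
- **Use of the words.** Table 5 is introduced by "Cue words that will be used in the assessments and training are shown in Table 5". The section on reminiscence therapy combined with memory specificity training describes prompts (details, senses, identity, positive themes, planning) applied to episodes that participants recall. It mentions no cue words.
- **Scoring.** Two scorers classify each response as "specific memory, generalized memory, vocabulary association or nonrecollection and nonresponse". The same sentence then states that "the scoring will be based on the number of cue words recalled by the participants".
- **Hypothesis.** The Background predicts that participants in the combined arm "will report improved autobiographical memory specificity", compared with both other arms, and that the gains will last 6 months.

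**The concern.** Depressive symptoms (GDS) are the primary outcome, and nothing here touches them. The memory test is secondary, but the Background makes better autobiographical memory the route by which depression should improve, and Study Design names it first among the effects to be assessed. An unclear memory score therefore weakens the test of the trial's explanation.

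Four features are at issue: the number of words, the reuse of one list, the stated use of the words in training, and the definition of the score. They do not carry equal weight. The first two follow from a direct count. The last two are real ambiguities whose consequences depend on how the text is read.

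**Working it through.** **1. Words per list.** The text gives 5 + 5 + 5 = 15. Counting Table 5 by column gives 9, 9 and 9, which is 27 distinct words with none repeated across columns. The stated 15 is not reproduced: each list has 15 − 9 = 6 fewer words, and 9/15 = 60% of the described length. The score range is 0–15 or 0–9, and one word is worth 1/15 = 6.7 or 1/9 = 11.1 percentage points.

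As an illustration of what length can mean for reliability, the Spearman–Brown formula with k = 9/15 = 0.6 is r' = 0.6r / (1 − 0.4r). The documents give no 15-word reliability r for this score, so these values are assumed:

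| Assumed r, 15 words | r', 9 words |
|---|---|
| 0.6 | 0.47 |
| 0.7 | 0.58 |
| 0.8 | 0.71 |
| 0.9 | 0.84 |

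This is a loss only if 15 words were intended.

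**2. Lists against occasions.** Table 4 has 5 test occasions; Table 5 has 3 lists. Baseline and post-intervention take one each, so the single follow-up list must serve T2, T3 and T4. A separate list for every occasion would need 5 × 9 = 45 words, or 5 × 15 = 75, against the 27 printed.

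Because lists are also fixed to occasions, a change in mean score over time mixes true change with list difficulty and, at T3 and T4, with having met the words before. As printed, every arm gets the same list at the same visit, so these effects are shared. They enter the within-group before–after results planned under Statistical analysis and the reading of maintenance to 6 months. They do not by themselves shift the difference between arms.

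**3. Assessment and training.** Three statements must be set side by side:

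- The sentence introducing Table 5 assigns its words to both uses.
- Table 5 has no training column and marks no word as a training word.
- The intervention section describes training by prompts, without cue words.

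The Background does describe memory specificity training as working through cues for recall, so a cue-word element is not far-fetched. If Table 5 words were used in training, only the combined arm would practise them. That effect would be differential, unlike the one in step 2. The number of words affected is not given, so no size can be attached.

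**4. Score.** Let S be the number of cues answered with a specific memory and G the number answered with a generalized one. Read literally, the number of cue words recalled is S + G. If m cues move from generalized to specific, S + G becomes (S + m) + (G − m) = S + G, which is unchanged, while S rises by m. The literal score would therefore not register the hypothesised shift from overgeneral to specific memory; a count of S would.

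**The case against.** **The 15 may describe the original instrument.** The figure stands in the sentence introducing the test as first developed, and the article then says a Chinese version will be used. The columns can be read as three positive, three neutral and three negative words, which would suggest a deliberate 9-word form. This is plausible and largely stands: a shorter test is not shown to be a mistake. But Table 5 carries no valence labels and the article nowhere says that a 9-word form is used.

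**Rehearsal of test words is not established.** A reader might infer that the combined arm will be drilled on the words it is tested on. The documents do not support that: the described training uses no cue words, and the reference to training may mean the two neutral practice words given before the test, or be stray wording. The objection stands against the inference, but not against the need to reconcile the sections.

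**The classification implies a specificity count.** A reader might infer that someone giving only overgeneral memories is certain to obtain the maximum score. That goes too far. Having two scorers sort responses into four categories would serve little purpose if the categories were ignored, and a count per category is a natural reading. The classified data would also yield the specific count directly. So the score is ambiguous, not shown to ignore specificity. Detailed scoring may sit in a fuller protocol, but this article does print a scoring rule, and that rule names no category.

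**The shared list and fixed order affect all arms.** This stands, and the hypothesis is mainly comparative. Rotating list order is therefore a preference, not the correction of an error.

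**Conclusion.** The point holds as an inconsistency in specification. A reader might conclude that the memory outcome is invalid as a whole; the documents do not show that.

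- **Firm, by count:** 15 words in the text against 9 per list, and one list for three follow-up tests. The repetition mainly blurs the time course and the 6-month maintenance claim.
- **Conditional:** if the sentence on training is meant literally, the comparison of the combined arm with reminiscence alone and with usual care would be biased in favour of the combined arm, by an amount that cannot be computed from the article.
- **Ambiguous:** two analysts could compute different scores from the same classified responses, and one of those scores would not measure the hypothesised specificity.

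This rests on the article alone and on Tables 4 and 5 being complete as printed. The change should be made because it is cheap and the outcome carries the mechanism hypothesis.

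**What to change.** 1. State how many positive, neutral and negative words this trial uses per occasion, label valence in Table 5, and make text and table agree. If the 15 refers only to the original test, one sentence saying so is enough.
2. Reconcile the Autobiographical memory section with the description of the training, and state that no test word is used in training. If the reference is to practice words, say so and list them separately.
3. Supply separate valence-matched lists for T2, T3 and T4 from the Chinese word database already cited. At 9 words per list this means two further lists, 2 × 9 = 18 words. At 15 per list across five occasions it means 75 − 27 = 48 further words.
4. Define the score as the number (or proportion) of cues answered with a specific memory, with the overgeneral count as a second score.

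Rotating list order across participants, equally in all arms, is optional and would separate list difficulty from time. The cost is slightly more list preparation and a few reworded sentences. Sample size, visits and the primary outcome are unaffected.

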Reminiscence therapy, as a potential psychological intervention to improve depressive symptoms in older adults, has an important therapeutic aspect of enhancing autobiographical memory and is often used interchangeably in the literature due to its similarity to the term “life review intervention” [24]. It enhances older people’s positive affect [25], cognitive functioning [26], social participation [27], quality of life, and ability to adapt to ageing [28] through the recall, narration, and reflection of past experiences. In addition to previous meta-analyses showing the significant effect of reminiscence-based interventions in improving psychological problems and enhancing well-being in older adults [29–31], there are also empirical studies showing that when researchers guided older adults through interventions for reminiscence at different stages of life, the older adults became more resistant to social stress, increased their ability to think and act for themselves, and finally, experienced completeness in the final stages of life [32–34]. However, in terms of the improvement of autobiographical memory, studies have shown that reminiscence therapy is not effective in improving it [35–37], possibly because reminiscence therapy is an inherent normative process of thinking about the past [38], rather than the practice and improvement of specific event details, which cannot significantly improve the effect of autobiographical memory.

Memory-specific training (MeST), as an intervention for improving autobiographical memory in some patients with mood disorders, has a good effect on patients’ difficulties in recalling personal events through the use of clues to recall words. Although MeST is simple and can be implemented singly, the effect is not good [39, 40]; thus, it can also be implemented together with traditional interventions such as reminiscence therapy as an adjunct therapy [40]. Consequently, there have been many studies combining these two therapies.

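### The protocol says the Table 5 test words also serve the training, while its intervention section describes training without cue words; if later test words were used, the memory comparison could favour RT-MeST

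*Protocol article*

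**What the plan says.** The protocol article measures autobiographical memory with a cue-word test at T0 to T4 (Table 4). Its Autobiographical memory section describes the test as containing "five positive cue words, five neutral words, and five negative cue words" and adds: "Participants will be given two neutral practice words to practice before the formal test". It then introduces the word table: "Cue words that will be used in the assessments and training are shown in Table 5". The columns of Table 5 are headed "pre-test post-test follow-up". No column is headed training or practice.

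The intervention is described elsewhere. Under Intervention, the content of the sessions comes from interviews held with participants beforehand. Under Reminiscence therapy and Table 2, the four weekly sessions follow life stages. The combined arm receives the same sessions with one addition: "the researcher will help participants to make their recollections more specific and complete when they recall a particular episode". The tools for this are listed after the words "Prompts that guide recall draw on other research [49] and cover the following areas": factual details, the senses, identity, positive themes, their generalisation, and future planning. None of these sections mentions a cue word.

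The Background describes memory specificity training in general as working "through the use of clues to recall words".

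**The concern.** The sentence that introduces Table 5 gives one set of words two uses, and every word in the table is assigned to a test occasion. Taken literally, any cue word used in training is also a word of the outcome test. Memory specificity training is given only to the combined arm during the four-week intervention, so exposure to test items would fall on that arm alone.

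The test classes a response as specific, generalised and so on. The training coaches residents towards specific responses. Coaching on a word that is scored later would rehearse a scorable answer to that word. The between-arm difference would then mix a general gain in memory specificity with remembered answers to practised items. Residents on reminiscence therapy alone or usual care would meet the words for the first time at the test.

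The Background hypothesises better memory specificity with the combined therapy than with either comparator, and treats this as the route to lower depression. A contaminated memory score would weaken that argument even if the GDS result stood.

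**Working it through.** The plan gives no figure to reproduce, so the check sets the passages side by side and counts words.

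**1. What each part of the article implies about cue words in training**

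| Place | Content | Implication |
|---|---|---|
| Autobiographical memory, sentence before Table 5 | Words serve assessments and training | Cue words are used in training, and they are Table 5 words |
| Table 5 | Three test-occasion columns | No word is assigned to training or barred from it |
| Intervention | Content from pre-interviews | No cue words |
| Reminiscence therapy, Table 2 | Sessions by life stage | No cue words |
| Reminiscence therapy combined with memory specificity training | Same sessions plus generic prompts | No cue words |
| Background | MeST in general relies on cues | Cue-word training is plausible, but this does not describe the trial's sessions |

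The first row conflicts with the three intervention rows. No statement in the article resolves the conflict.

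**2. Count of Table 5**

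- Words per column: 9, 9 and 9. Total 9 + 9 + 9 = 27.
- Words shared between any two columns: 0, so all 27 are distinct.
- The text describes 5 + 5 + 5 = 15 words per test, against 9 listed. This is a separate discrepancy. Here it means only that the counts below refer to the listed words.

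**3. Possible exposure of the RT-MeST arm**

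| Words used in sessions | Post-test words rehearsed | Follow-up words rehearsed |
|---|---|---|
| None | 0 of 9 | 0 of 9 |
| Pre-test list only | 0 of 9 | 0 of 9 |
| Post-test list | up to 9 of 9 | 0 of 9 |
| Follow-up list | 0 of 9 | up to 9 of 9 |
| Post-test and follow-up lists | up to 9 of 9 | up to 9 of 9 |

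The first two rows give no rehearsal of any item tested after the intervention. The last three do.

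**4. Size**

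To turn exposure into a difference in scores, one would need the number of words rehearsed, the chance of a specific answer with and without rehearsal, and the spread of scores between residents. The article gives none of these. Any standardised effect would therefore be assumed throughout, so none is offered. The lower end of the range is zero.

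**The case against.** A reader might infer that the combined arm will be drilled on the test and that its memory advantage is built in. The documents do not support that, for these reasons:

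- The section that says what participants receive uses generic prompts and no cue words. If sessions run as described there, no item is shared and nothing is rehearsed. The form of the sessions therefore decides the matter.
- The Background sentence on cues describes memory specificity training in general and cannot override the trial's own intervention section.
- Table 5 uses fresh words at each stage, which suggests that the authors wanted to avoid item effects.
- Rehearsal of scored words would require post-test or follow-up words in the sessions, and nothing says so.
- The word *training* may be loose wording, or may refer to the practice before the test.

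Most of this stands, and it rules out a claim of established bias. It does not remove the conflict. Non-overlapping columns protect against carry-over from one test to the next, but not against exposure in sessions, because no column is barred from training. The practice-word reading fits poorly: the article calls those words practice words, says that both are neutral, and shows no such entry in Table 5. If that was the intent, the sentence still needs correcting.

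A reader might also compare a supposed bias with the planning effect of 0.8. The Sample size calculation section does not tie that figure to autobiographical memory, so the comparison has no basis.

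**Conclusion.** The point holds as an internal contradiction with a conditional risk of bias. The Autobiographical memory section assigns test words to training as well as assessment; the intervention sections describe training without cue words. If the former is followed with post-test or follow-up words, only the RT-MeST arm is exposed to outcome items, and the memory comparison could be biased in its favour against both other arms.

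The magnitude is unknown. Between 0 and 9 of the 9 listed words in each later list could be affected, and the bias is zero if no word tested from T1 to T4 is used as a training cue. The direction rests on the assumption that coaching on a word makes a specific answer to that word more likely at the test.

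The reach is limited to a secondary outcome and the mechanism hypothesis. GDS scores do not depend on these words. It is still more than a missing detail, because the article states a rule which, if followed, could undermine that outcome, and exposure cannot be undone once sessions have used the words.

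**What to change.** Reconcile the sentence before Table 5 with the intervention sections in one of two ways:

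1. If sessions use no cue words, delete *and training* and state that Table 5 words are used in assessments only.
2. If sessions do use cue words, say so in the section on the combined therapy. Give a separate training list with no word in common with any assessment list, and state that assessment words are not used as training cues.

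The restriction should cover deliberate use as cues only. Forbidding implementers to say ordinary words such as *Books* or *History* in free group recall about study and education would be impractical and is not needed.

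The cost is one sentence under the first option. The second adds a short word list, which could be drawn from the Chinese vocabulary database that the article already mentions. Neither changes the sample size, the visits or the analysis.
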